### Primary Outcomes

This study will be divided into two stages. In the cross-sectional study, our primary outcome was BMD. In the follow-up period, an osteoporotic fracture is the most crucial outcome. Although important information on new fractures will be obtained through the self-reports of participants or interviews during the follow-up, we will immediately re-evaluate and confirm the bone mass of patients with new fracture events based on DEXA. Patients who suffer from fractures will be asked to describe when and why they occurred, their fracture site, and treatment after the fracture.

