This prospective study will investigate conventional risk factors and relevant symptoms as reported in traditional Chinese medicine (TCM) in populations with a high risk of postmenopausal osteoporosis (18, 19). Based on the findings of this preliminary study, we will then conduct a further cross-sectional survey and a prospective follow-up study in the Beijing community. The present prospective study aims to investigate the prevalence of OP and the incidence of osteoporotic fracture in Beijing community residents to further explore the risk factors related to this condition and to put forward some rational suggestions for patients. This research on “Beijing community-based Osteoporosis and osteoporotic fracture screening: a cross-sectional and prospective study (beyond)” will provide reliable data for the prevention of OP and osteoporotic fractures among community-dwellers in the Beijing area.

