### Bone Density Screening

A dual-energy X-ray absorptiometry (DEXA) device (HOLOGIC Wi, United States) will be used to detect the lumbar spine and bilateral hips and to record the *T* and *Z*-values of each site. The precision of the instrument will be set at 1%, that is, the error of repeated measurement will be <1%. After using the instrument every day, professional staff will be responsible for checking accuracy and maintenance.

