### Collecting Clinical Information

All participants will complete a face-to-face paper version of the questionnaire and undergo a comprehensive physical examination. The questionnaire and examination will mainly assess the general characteristics of participants, menstrual status, menopausal age, number of pregnancies, number of births, education level, income level, history of smoking and drinking, history of previous illness and medication, number of falls, daily dietary habits, TCM syndrome, and so on. Information on various fractures, such as the number, cause, location, and therapeutic method, will be recorded in detail. The questionnaire will also include the International Physical Activity Questionnaire (21), the 1 Min Osteoporosis Risk Assessment Test of the International Osteoporosis Foundation (22), and the EuroQol 5-dimension instrument (23) to evaluate the physical activity and quality of life of participants.

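### Follow-up fractures are known only from what participants report, so the study will estimate the incidence of clinically recognised fracture, not of all osteoporotic fracture as stated

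*Protocol article*

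**What the plan says.** The Introduction of the protocol article gives one aim as "the incidence of osteoporotic fracture in Beijing community residents". The Abstract and Discussion describe the follow-up result in the same unqualified terms.

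Under Primary Outcomes the outcome is a single item: "In the follow-up period, an osteoporotic fracture is the most crucial outcome". On how events come to light, the section says that "important information on new fractures will be obtained through the self-reports of participants or interviews during the follow-up". The verification step is "we will immediately re-evaluate and confirm the bone mass of patients with new fracture events based on DEXA". The details of each event come from the participant: "Patients who suffer from fractures will be asked to describe when and why they occurred, their fracture site, and treatment after the fracture".

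The only imaging described is the DEXA in Bone Density Screening, which "will be used to detect the lumbar spine and bilateral hips and to record the" T and Z values of each site. Collecting Clinical Information adds that "Information on various fractures, such as the number, cause, location, and therapeutic method, will be recorded in detail".

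The Discussion lists three limitations: restricted external validity, unequal sex or age groups, and recall bias in questions about past illness and medication. Missed incident fractures are not among them.

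**The concern.** The stated claim is wider than the stated method can support. If some vertebral fractures pass without a recognised event, a participant who attends every contact and answers truthfully still cannot report them. The DEXA step does not close the gap, because it starts from a known fracture and measures bone mass. Nor can later analysis of the collected data recover events that were never observed.

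Two uses of the result are at stake. First, both the Introduction and the Discussion stress that fracture epidemiology differs between regions, so a Beijing figure invites comparison. Set against a study that images the spine in everyone, part of any difference would come from the method. Second, the Discussion plans to explore factors that influence fracture. Those analyses will concern recognised fractures, and factors for silent vertebral fractures stay out of view.

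**Working it through.** **The plan's own figure.** The article gives no expected fracture rate. Its only planning number is at least 1,500 participants from a power analysis whose inputs are not stated (Materials and Methods), so it cannot be reproduced. A precision formula, n = 1.96² p(1−p)/d², with the 9.65% osteoporosis prevalence from the Introduction and an assumed d of 1.5 percentage points, gives 3.8416 × 0.0965 × 0.9035 / 0.015² ≈ 1,489. But d is a guess and the formula concerns prevalence. The present point does not depend on it; 1,500 is used below only as the cohort size.

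**Step 1: can an unrecognised vertebral fracture enter the outcome?**
- Entry route: self-report or interview. It requires that the participant knows of the fracture.
- DEXA after an event: applies only to people already counted, and checks bone mass.
- Screening DEXA: lumbar spine and hips, for T and Z values; no assessment of vertebral shape is stated.

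None of the three would record it.

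**Step 2: share missed.** Let v be the vertebral share of true osteoporotic fractures and s the silent share of those. Both are assumptions; the article gives neither. Non-vertebral fractures are taken as fully reported and false reports are ignored.

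Share missed = v × s.
- Low end: 0.20 × 0.30 = 0.06
- High end: 0.50 × 0.75 = 0.375

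So about 6% to 38% of true fractures are missed, and 94% down to 62.5% are captured. If s were 0, nothing would be missed.

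**Step 3: what that means at 1,500 participants.** Let R be the true two-year risk (also assumed), counting one fracture per person. Observed risk = R(1 − vs). The half-width of the 95% interval is 1.96 × √(p(1−p)/1500) at the observed risk p, without allowance for dropout or clustering. Each range runs from the low to the high end of Step 2.

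| R | True fractures | Missed | Observed risk | Shortfall (points) | Half-width (points) |
|---|---|---|---|---|---|
| 2% | 30 | 1.8 to 11.3 | 1.88% to 1.25% | 0.12 to 0.75 | 0.69 to 0.56 |
| 4% | 60 | 3.6 to 22.5 | 3.76% to 2.50% | 0.24 to 1.50 | 0.96 to 0.79 |
| 6% | 90 | 5.4 to 33.8 | 5.64% to 3.75% | 0.36 to 2.25 | 1.17 to 0.96 |

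At the low end the shortfall is well inside sampling error; at the high end it exceeds it at every assumed risk.

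**Step 4: effect on a risk ratio.** Take a vertebral share of 0.4, a true ratio of 2.0 at all sites, and spine detection d1 in people with osteoporosis and d0 in others:

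observed ratio = (0.6 × 2 + 0.4 × 2 × d1) / (0.6 + 0.4 × d0).

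- d1 = d0 = d: the ratio is exactly 2.0 for any d.
- d1 = 0.50, d0 = 0.25: 1.6 / 0.7 = 2.29.

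Inflation therefore needs unequal detection. Under-capture alone does not produce it.

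**The case against.** The strongest reply is that much of the criticism can be pushed further than the article allows. Four parts of that reply stand.

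- **Pooling.** A reader might infer that all sites will be merged in one analysis. The article names one undivided outcome but never says that sites will be combined, and the site of each fracture is recorded. Tabulation by site is a detail that a condensed article may leave to a fuller document.
- **Inflated association with bone density.** A reader might infer that participants with low bone density will have more silent fractures found. That requires that they are told their result, have more spine imaging outside the study, and have incident fractures found by it. The article states none of these, and with equal detection the ratio is unchanged (Step 4).
- **Size and net direction.** The vertebral and silent shares are assumptions. The article describes no confirmation that a reported event was a fracture, or a fragility fracture, so false reports could offset part of the loss.
- **A non-vertebral headline endpoint.** This would discard recognised vertebral fractures. As a share of counted events they are v(1−s)/(1−vs), which over the assumed ranges runs from 0.05/0.85 = 6% to 0.35/0.85 = 41%. That is a heavy price in a cohort of this size.

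What does not stand is the suggestion that this is only a detail left out of a condensed article. The article states both how fractures are ascertained and what the result will be called, and the second is wider than the first.

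**Conclusion.** The point holds in a limited form. As described, the follow-up yields the incidence of self-reported, clinically recognised osteoporotic fracture. Vertebral fractures that participants do not recognise are outside the count, and the limitations do not say so. This conclusion follows from the text and needs no outside figure beyond the premise that some vertebral fractures go unrecognised.

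The amount missed is not determinable from the article. The 6-38% range is an illustration resting on an assumed vertebral share of 20-50%, an assumed silent share of 30-75%, and full reporting at other sites. Bias in the risk-factor associations through unequal detection is possible but not shown.

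It would also go too far to say that the figure cannot be called an incidence at all: it is a valid incidence of a narrower event, and needs that qualification.

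**What to change.** 1. In the Abstract, Introduction, Primary Outcomes and Discussion, define and report the follow-up outcome as clinically recognised (self-reported) osteoporotic fracture.
2. Keep all recognised fractures as the main outcome. Use the recorded site to report vertebral and non-vertebral incidence separately, and label the vertebral figure a lower bound.
3. Repeat the risk-factor analysis on non-vertebral fractures as a sensitivity analysis. Similar results would suggest that uneven spine detection is not driving the findings; different results would call for caution.
4. Add under-ascertainment of vertebral fractures to the limitations in the Discussion.

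The cost is a narrower claim and a little more analysis, with fewer events in the sensitivity analysis. No added imaging, visit or data field is needed.

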### Follow-up Study

A subsequent follow-up study will be conducted annually until December 2020.

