### Data Management and Statistical Analysis

Data will be recorded in the case report form (CRF), and it will be reviewed and validated by researchers, data managers, and statisticians for final statistical analysis at the end of this study. The CRF will be entered into Epidata 3.1 software by two researchers independently, and the recorded data will be checked for consistency. If there are inconsistencies, the CRF or other original records will be carefully verified. The data will be modified one by one until the independently entered data are identical. The data administrator will further check the exported database and use a logic check to check data until and doubts are resolved. The electronic database will eventually be locked.

IBM SPSS version 22.0 (SPSS, Chicago, IL, United States) software will be used to analyze the data. Continuous data will be analyzed using the independent *t*-test or Wilcoxon's rank sum test, while categorical data will be compared using the chi-square or Fisher's exact test. All statistical analysis tests will be performed using a two-sided hypothesis test. The *P* ≤ 0.05, and the difference in the test will be considered statistically significant. We will also adjust the correlation analyses for factors such as age, gender, and comorbidities.

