## Discussion

OP is characterized by low bone mass and microstructured bone tissue degradation (24). The high mortality and morbidity of osteoporotic fractures make them a serious public health threat (25, 26). The incidence and prevalence of fractures also varies across geographic regions and countries (27–30). Therefore, it is important to develop specific and preventive measures. Additionally, the prevalence of OP and associated fractures in the Beijing community has received little attention. The relatively large sample size of the research allows for a systematic investigation of the risk factors associated with OP via the cross-sectional study, including TCM syndrome differentiation and functional activity, which few community studies have previously investigated. Based on the follow-up of fracture outcome, this research will also dynamically monitor the incidence of osteoporotic fractures and explore the influencing factors of osteoporotic fractures in depth through a comprehensive survey.

This study also has several limitations. First, this study may have limited external validity, as it will only include the participants from some districts in the Beijing area. Second, the final results may be influenced by unequal numbers of gender or age groups in the real-world setting, so the clinical practical value will be lower than that of randomized controlled trials. Third, recall bias may arise from some of the retrospective questions, such as patient history relating to previous illness and medication (31). In summary, more useful information on the prevention and control of OP and associated fractures will be beneficial to improving the management of healthcare in the Beijing community.

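### The one confirmation step stated for reported new fractures is DEXA, which checks bone mass and not whether or where a fracture occurred

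*Protocol article*

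**What the plan says.** The Primary Outcomes section sets the follow-up endpoint: "In the follow-up period, an osteoporotic fracture is the most crucial outcome". On where events come from, it says that "important information on new fractures will be obtained through the self-reports of participants or interviews during the follow-up". That clause begins with a concession (although), and the main clause gives the response: "we will immediately re-evaluate and confirm the bone mass of patients with new fracture events based on DEXA". The remaining detail is again the participant's own account: "Patients who suffer from fractures will be asked to describe when and why they occurred, their fracture site, and treatment after the fracture".

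Three other sections bear on the point:

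- **Bone Density Screening** describes what DEXA does in this study. It "will be used to detect the lumbar spine and bilateral hips and to record the" T and Z values of each site. No fracture imaging is mentioned.
- **Follow-up Study** sets the contact schedule: "A subsequent follow-up study will be conducted annually until December 2020".
- **Data Management and Statistical Analysis** mentions source records once, for mismatches between two independent data entries: "If there are inconsistencies, the CRF or other original records will be carefully verified".

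**The concern.** The sentence concedes that self-report is a limited source and then offers a check that does not address the limitation. A DEXA measurement of bone density does not show whether a reported injury was a fracture, a sprain or an old deformity. The measured sites, lumbar spine and hips, do not include the wrist, humerus or other limb sites.

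This matters because fracture is likely to be uncommon over about two years. When true events are few, even a small false-report rate in the large fracture-free majority can make up a sizeable share of the counted events. The incidence of osteoporotic fracture and the factors that influence it are stated aims of the study, and both rest on this count. Participants also have their bone density measured at baseline. Those who learn that it is low may be readier to call an injury a fracture, which would tie the error to the study's central exposure.

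**Working it through.** **Step 1. Is there another check?** The sections side by side:

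| Section | What is checked | Shows that a fracture occurred? |
|---|---|---|
| Primary Outcomes | bone mass, by DEXA | no |
| Bone Density Screening | T and Z values, lumbar spine and hips | no |
| Collecting Clinical Information | fracture number, cause, location and therapy, by questionnaire and examination; no source record named | no |
| Data Management and Statistical Analysis | agreement of two data entries | no: a false report entered identically twice passes |

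**Step 2. Inputs.** The article gives N of at least 1,500 and follow-up of at least 2 years (Materials and Methods). It gives no fracture incidence, reporting sensitivity, false-report rate or effect size, so there is no figure of its own to reproduce. The following are assumptions:

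- true 2-year risk i = 1, 2 or 4%;
- 90% of true fractures reported;
- false-report rate f = 0.25, 0.5 or 1% over 2 years among the fracture-free;
- 50% exposed, true risk ratio 2.0, hence i0 = 2i/3 (unexposed) and i1 = 4i/3 (exposed);
- the same error rates in both groups.

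**Step 3. Formulas.**

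- True events counted: T = 1,500 × i × 0.9
- False events counted: F = 1,500 × (1 − i) × f
- Share real = T / (T + F); observed incidence = (T + F) / 1,500
- Observed risk ratio = [0.9·i1 + (1 − i1)·f] / [0.9·i0 + (1 − i0)·f]

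**Step 4. Central case (i = 2%, f = 0.5%).** T = 27 and F = 7.35, so the share real is 27 / 34.35 = 79%. Observed incidence is 2.29% against 2%. With i0 = 1.333% and i1 = 2.667%, the risk ratio is 0.02887 / 0.01693 = 1.70.

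**Step 5. Full grid.**

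| i | f | T | F | Share real | Observed incidence | Observed risk ratio |
|---|---|---|---|---|---|---|
| 1% | 0.25% | 13.5 | 3.7 | 78% | 1.15% | 1.71 |
| 1% | 0.5% | 13.5 | 7.4 | 65% | 1.40% | 1.54 |
| 1% | 1% | 13.5 | 14.9 | 48% | 1.89% | 1.37 |
| 2% | 0.25% | 27 | 3.7 | 88% | 2.05% | 1.83 |
| 2% | 0.5% | 27 | 7.4 | 79% | 2.29% | 1.70 |
| 2% | 1% | 27 | 14.7 | 65% | 2.78% | 1.54 |
| 4% | 0.25% | 54 | 3.6 | 94% | 3.84% | 1.91 |
| 4% | 0.5% | 54 | 7.2 | 88% | 4.08% | 1.83 |
| 4% | 1% | 54 | 14.4 | 79% | 4.56% | 1.70 |

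In eight of the nine cells the observed incidence is too high. At i = 4%, f = 0.25% it is 3.84%, which is too low.

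**Step 6. If the error depends on the risk factor.** Here all true fractures are assumed reported, with a false-report rate of 2% in the exposed and 0.5% in the unexposed. A true risk ratio of 1.0 at a true risk of 2% becomes (0.02 + 0.02 × 0.98) / (0.02 + 0.005 × 0.98) = 0.0396 / 0.0249 = 1.59. At true risks of 3% and 5% it becomes 1.42 and 1.26. With 30% exposed, a true risk ratio of 2.0 becomes 2.47, 2.33 and 2.20 at true risks of 2%, 3% and 5%.

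**The case against.** The strongest reply is that an article condenses a fuller protocol, and that event verification is commonly left to that document or the CRF. The text does not say that self-report is the only source, nor does it rule out checking records. This stands as a limit: one can say only that no such check is stated. It does not remove the point, because the article does not simply stay silent. It names a safeguard against the weakness of self-report, and that safeguard measures something else.

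A second reply is that DEXA may be meant to classify a fracture as osteoporotic rather than to verify it. That reading is possible and would be a sensible use of the scan. It still leaves the occurrence and site of the fracture unchecked.

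A reader might also infer more than the document supports:

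- **That every risk-factor estimate is diluted.** The cross-sectional analyses use BMD and are not touched. Dilution of the fracture estimates needs error unrelated to the risk factor; Step 6 shows that the bias can run the other way.
- **That incidence is inflated.** One cell of the grid contradicts this, and more under-reporting would lower the count further. In the central case, about 34 counted against 30 true events is also within sampling error: the exact Poisson 95% interval for 30 events is about 20 to 43.
- **That the authors concede the problem in their limitations.** The Discussion says that "recall bias may arise from some of the retrospective questions", but its example is past illness and medication. It does not name the fracture outcome.

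Finally, every rate is assumed, and the range runs from serious to minor.

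**Conclusion.** The point holds in limited form. As written, the stated confirmation step for new fractures verifies bone mass, and nothing shown verifies the fracture or its site. The follow-up incidence may be biased in either direction. The fracture risk-factor estimates may be biased towards the null under non-differential error, or away from it if participants told of low bone mass over-report.

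Under the Step 2 assumptions, between about half and nearly all reported fractures are real (48–94%), and a true risk ratio of 2.0 appears as 1.37–1.91. These figures show sensitivity to plausible error rates; they do not estimate the error in this study. The change is worth making because the follow-up endpoint depends on it and the cost is small.

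**What to change.** In Primary Outcomes, describe DEXA as recording bone status after a fracture, not as the check on self-report. For each reported fracture, request the existing X-ray report, discharge summary or outpatient record, and take site and date from it. Use record-confirmed fractures as the primary follow-up outcome. Report all self-reported fractures as a sensitivity analysis, and state how many had no retrievable record.

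Removing false reports restores the risk ratio if the share of true fractures confirmed is equal across exposure groups: with f = 0 the 0.9 cancels and the ratio is i1 / i0 = 2.0.

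The cost is one extra CRF item and a document request for roughly 17 to 68 participants on the assumed grid (T + F, taking one report per person). No new imaging is needed. The counted events may fall noticeably: by 6–52% on the grid if every true reported fracture has a record. True fractures without records would be left out of the confirmed count, and fractures never reported stay missed. In the central case the count goes from about 34 to 27 against 30 true, so the confirmed incidence would be somewhat low. That is why both counts should be reported.

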### Data Management and Statistical Analysis

Data will be recorded in the case report form (CRF), and it will be reviewed and validated by researchers, data managers, and statisticians for final statistical analysis at the end of this study. The CRF will be entered into Epidata 3.1 software by two researchers independently, and the recorded data will be checked for consistency. If there are inconsistencies, the CRF or other original records will be carefully verified. The data will be modified one by one until the independently entered data are identical. The data administrator will further check the exported database and use a logic check to check data until and doubts are resolved. The electronic database will eventually be locked.

IBM SPSS version 22.0 (SPSS, Chicago, IL, United States) software will be used to analyze the data. Continuous data will be analyzed using the independent *t*-test or Wilcoxon's rank sum test, while categorical data will be compared using the chi-square or Fisher's exact test. All statistical analysis tests will be performed using a two-sided hypothesis test. The *P* ≤ 0.05, and the difference in the test will be considered statistically significant. We will also adjust the correlation analyses for factors such as age, gender, and comorbidities.

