## Abstract

**Background:** Osteoporosis (OP) patients are usually asymptomatic until osteoporotic fractures occur, which makes early diagnosis and prevention difficult, and the associated fractures secondary to OP could be preventable with appropriate management. Therefore, early identification and relevant evidence-based management of OP could guide the prevention of subsequent fractures. This study will investigate the prevalence of OP and the incidence of osteoporotic fractures in Beijing community residents to further explore the related risk factors and put forward suggestions for people aged 45–80 years old.

**Methods:** Over 2 years, this study will conduct an OP screening and a prospective follow-up in the Beijing community to investigate the incidence of osteoporotic fractures. The study will undertake bone mineral density detection, collect biological samples, and record information via questionnaires.

**Discussion:** The study aims to investigate the potential risk factors for osteoporosis and explore syndromes from traditional Chinese medicine that are associated with this condition based on large samples from the Beijing community. Data on the incidence of osteoporotic fractures among community dwellers in Beijing over the two-years will be available on the Chinese clinical trial registry: ChiCTR-SOC-17013090.

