## Materials and Methods

This is a community-based cross-sectional and prospective follow-up study. Based on the different economic conditions in Beijing, we will seek residents from several districts from people who respond to an invitation to participate. Then, the participants will be screened, based on predetermined inclusion and exclusion criteria, and an epidemiological investigation will be conducted. The investigation will gather data on BMD screening, biological samples, and questionnaire information. Each participant will be followed for at least 2 years to track incidences of osteoporotic fracture. Based on a power analysis, the required sample size will be at least 1,500 patients. A flow chart of the research process is shown in Figure 1.

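### The only named tests ignore time at risk, although follow-up can differ between participants; applied to fracture they can mislead

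*Protocol article*

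**What the plan says.** All references are to the protocol article.

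- **Length of follow-up.** Materials and Methods sets a minimum: "Each participant will be followed for at least 2 years to track incidences of osteoporotic fracture". Follow-up Study sets a common calendar end: "A subsequent follow-up study will be conducted annually until December 2020". The Abstract describes the result as a two-year figure: "Data on the incidence of osteoporotic fractures among community dwellers in Beijing over the two-years".
- **Outcome and aim.** Primary Outcomes states: "In the follow-up period, an osteoporotic fracture is the most crucial outcome". The Discussion says the study will "dynamically monitor the incidence of osteoporotic fractures and explore the influencing factors of osteoporotic fractures in depth".
- **Timing of events.** Primary Outcomes also says: "Patients who suffer from fractures will be asked to describe when and why they occurred". The information needed to place a fracture in time is therefore requested.
- **Analysis.** Data Management and Statistical Analysis names tests by type of data: t or Wilcoxon tests for continuous data, while "categorical data will be compared using the chi-square" or Fisher's exact test. Tests are two-sided at 0.05. One further sentence adds adjustment of correlation analyses for factors such as age, gender and comorbidities. It names no model and does not mention follow-up.

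**The concern.** A minimum duration combined with a common end date means that a participant who enters earlier can be observed for longer. Death and loss to follow-up add further variation. Fracture is an event that accumulates with time, so the proportion ever fractured depends on how long people were watched as well as on their risk.

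The named tests compare means, ranks or proportions and have no place for follow-up time. If they are applied to ever versus never fractured, two things are at stake. The incidence figure becomes a proportion over a mixture of durations, which cannot be compared with another study or with the Abstract's two-year description. And any factor related to length of follow-up can look like a risk factor for fracture when it is not. Entry date could be tied to such a factor if, for example, communities or districts were enrolled one after another.

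**Working it through.** **The plan's own figure.** The only design number is a sample size of at least 1,500. The article does not give the power, effect size, event rate or dropout behind it, so it cannot be reproduced. Nothing below depends on it, except that 750 per group is half of 1,500.

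**Inputs from the article.** Two-sided test at 0.05; minimum follow-up of 2 years; common end date.

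**Assumptions, not in the article.** Two groups of 750; the same constant fracture rate λ in both, at 0.5%, 1% or 2% per year; mean follow-up of 2 years in one group and 2, 2.5 or 3 years in the other. The article gives no fracture rates, enrolment dates or group sizes.

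**Formulas.** Cumulative risk after t years is p = 1 − exp(−λt). The chi-square test is equivalent to z = (p₂ − p₁) / √[p̄(1 − p̄)(1/750 + 1/750)], where p̄ is the mean of the two risks.

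**One case by hand (λ = 1% per year, 2 v 3 years).**

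1. p₁ = 1 − exp(−0.02) = 1.98%; p₂ = 1 − exp(−0.03) = 2.96%.
2. Risk ratio = 2.96 / 1.98 ≈ 1.49, although the true rates are equal.
3. p̄ ≈ 2.47%, so the standard error is √(0.0247 × 0.9753 × 2/750) ≈ 0.0080.
4. Expected z ≈ 0.00975 / 0.0080 ≈ 1.22.
5. Probability of rejection ≈ Φ(1.22 − 1.96) + Φ(−1.22 − 1.96) ≈ 0.23, against a nominal 0.05.

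**All cases, simulated.** The person-time column is a Wald test of the log rate ratio, using expected person-years in each group.

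| Rate per year | Follow-up (years) | Cumulative risks | Risk ratio | Chi-square rejects | Person-time test rejects |
|---|---|---|---|---|---|
| 0.5% | 2 v 2 | 1.00% v 1.00% | 1.00 | 4.6% | 3.4% |
| 0.5% | 2 v 2.5 | 1.00% v 1.24% | 1.25 | 7.1% | 3.4% |
| 0.5% | 2 v 3 | 1.00% v 1.49% | 1.50 | 13.7% | 3.9% |
| 1% | 2 v 2 | 1.98% v 1.98% | 1.00 | 5.1% | 4.2% |
| 1% | 2 v 2.5 | 1.98% v 2.47% | 1.25 | 9.7% | 4.3% |
| 1% | 2 v 3 | 1.98% v 2.96% | 1.49 | 22.9% | 4.2% |
| 2% | 2 v 2 | 3.92% v 3.92% | 1.00 | 5.0% | 4.2% |
| 2% | 2 v 2.5 | 3.92% v 4.88% | 1.24 | 14.6% | 4.5% |
| 2% | 2 v 3 | 3.92% v 5.82% | 1.49 | 40.2% | 4.2% |

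**The benign case.** If each person's follow-up is drawn uniformly between 2 and 3 years, independently of the factor, the chi-square test rejects in 5.3% of studies at both 1% and 2% per year. Unequal follow-up alone does not inflate the error rate; a difference in follow-up between the compared groups does.

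**The case against.** The strongest reply is that the article never says fracture will be analysed by chi-square. The sentence on tests is generic, sorts methods by data type, and serves a two-stage study with a large cross-sectional part. A further adjusted analysis is planned, and a condensed article may leave the incidence estimator, censoring rule and regression model to a fuller document. Part of this stands: a reader might infer that chi-square is expressly assigned to fracture, and the text does not support that. But the article did choose to name tests. None of them fits the follow-up it describes, no other method is named for the main follow-up outcome, and the factors listed for adjustment do not address time at risk.

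A second reply is that the Abstract's two-year description, the two-year minimum and the requested fracture dates together permit a fixed two-year risk. A chi-square test on that would avoid the problem, apart from loss and death. This is a plausible reading, but the methods define no such window, and follow-up to December 2020 can extend past it.

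Three stronger inferences should be resisted:

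- **Incidence will be biased downwards.** This would follow if people who die or are lost were counted as fracture-free. The article does not say how they are handled.
- **Fracture dates will go unused.** No named method uses them, but the article does not say that they will be ignored.
- **The district comparison will be distorted.** The article gives no enrolment dates and does not name a district comparison of fractures as an analysis. A one-year gap is illustrative.

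**Conclusion.** The concern holds in a conditional form. Time at risk can differ between participants, and the article names no method that takes account of it for the main outcome of the follow-up stage. Used on ever versus never fractured, the named tests would give an incidence figure with no single time base. They can produce false risk factors, but only where follow-up length differs between the groups being compared.

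Under the assumptions shown, with a true risk ratio of 1, the apparent ratio is about 1.5 with a one-year gap (about 14% to 40% false rejections) and about 1.25 with a half-year gap (about 7% to 15%). The error rate is about 5% if follow-up is unrelated to the factor. These figures show how the size depends on the gap and the rate; they do not predict what this study will find.

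**What to change.** In Data Management and Statistical Analysis, add a short paragraph on the follow-up stage stating that:

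1. Fracture incidence will be reported per 1,000 person-years with a Poisson confidence interval and, to match the Abstract, as 2-year cumulative incidence.
2. Risk factors for fracture will be analysed by Cox regression, or by Poisson regression with log person-time as an offset. Time runs from the baseline examination to the first reported osteoporotic fracture and is censored at death or last contact.
3. These models carry the adjustment already planned for age, gender and comorbidities.
4. The t, Wilcoxon, chi-square and Fisher tests are for the cross-sectional comparisons.

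Treating death as a competing event, adjusting for baseline bone density, or requiring confirmation of each fracture may be worth discussing, but this point does not depend on them.

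The cost is small: a change of wording, plus dates of last contact and death recorded at the annual contacts. Fracture timing is already to be asked for.
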